## Abstract

**Background:**

Acupuncture and moxibustion has been widely applied to hyperlipidemia treatment in clinical practice in China, serving as an alternative treatment to statins. Warm-needling acupuncture and medicinal cake-separated moxibustion have been separately reported with potential therapeutic effects on hyperlipidemia treatment in several studies but with limitations in study methodology. Combining these two modalities may provide a more advantageous strategy in treating hyperlipidemia. Therefore, a strict evaluation through well-designed randomized controlled trials (RCT) is necessary to determine their efficacy and safety on hyperlipidemia.

**Methods:**

The study a multicenter, open-label, randomized, stratified, active-controlled, noninferiority trial with two parallel groups. Subjects with hyperlipidemia will be stratified into different groups by risk levels of heart diseases. They then will be instructed to the Therapeutic Lifestyle Change (TLC) diet. Those who have not reached the target lipid level will be randomly assigned to the treatments of either acupuncture and moxibustion or simvastatin with a 1:1 allocation. One hundred and thirty subjects are aimed to be recruited. The duration of intervention for this study will be 12 weeks, followed by another 4 weeks for post-treatment assessment. The primary outcome is percentage change from baseline to the end of the study in low-density lipoprotein cholesterol (LDL-C). Other indicators in lipid change, safety and adherence will also be assessed secondarily. The repeated measures, linear mixed-effects model will be applied to the analysis.

**Discussion:**

Acupuncture and moxibustion could be a potentially effective treatment alternative for hyperlipidemia. A study with careful design is developed to evaluate the efficacy and safety of combined acupuncture and moxibustion, by integrating the traditional Chinese Medicine (TCM) regimens with the standardized Western medicine appraisal approach.

**Trial registration:**

ClinicalTrials.gov, NCT02269046. Registered on 26 September 2014.

**Electronic supplementary material:**

The online version of this article (doi:10.1186/s13063-017-2029-x) contains supplementary material, which is available to authorized users.

## Background

### Background and rationale

Hyperlipidemia refers to a condition caused by abnormal metabolism where low-density lipoprotein-cholesterol (LDL-C), serum total cholesterol (TC), triglycerides (TG), and/or high-density lipoprotein (HDL-C) are above recommended levels. This condition is associated with the deterioration in lifestyle and dietary habits and represents an important risk factor for cardiovascular morbidity and mortality. Hyperlipidemia is a risk factor for atherosclerosis, cardiovascular disease, stroke, and other diseases. Large randomized controlled trials in hyperlipidemia treatment have provided evidence that reducing LDL cholesterol concentration with statins is efficient in both secondary and primary cardiovascular disease (CVD) prevention [1, 2]. As a result, individuals at moderate or high CVD risk are often considered as candidates for lipid-lowering therapy with statins. However, statin therapy can incur significant cost to the society. In addition, statin therapy is often associated with low treatment compliance and high rates of side effects [3, 4].

Acupuncture and moxibustion has been widely applied to hyperlipidemia treatment in clinical practice of China. Thus, an increasing number of studies have explored whether acupuncture and moxibustion could serve as an alternative treatment for subjects with hyperlipidemia. As shown in a meta-analysis, acupuncture solely, compared to statins, has demonstrated a more significant effect on decreasing TG and increasing HDL-C, but no superiority in lowering the LDL-C and TC [5]. Meanwhile, moxibustion, which is often administered with acupuncture in Traditional Chinese Medicine (TCM) practice, also plays an essential role in lipid-lowering by warming meridians and facilitating lipid conversion in the TCM theory. The recent studies have further revealed the biological pathway in lipid-lowering of moxibustion [6–8]. This modality, especially the warm-needling acupuncture (acupuncture with a moxa stick), can enhance microcirculation, adjust the lipid metabolism, and thus lower the blood viscosity [6–8].

Medicinal cake-separated moxibustion, an important kind of moxibustion, applies the acupoints, moxibustion, and traditional Chinese herb in an integrative way. It has gained increasing popularity in the practice of hyperlipidemia treatment and thus been further assessed on its potential impact. Some findings have shown, from a perspective of gene transcription and protein expression, that the medicinal cake-separated moxibustion could prevent the formation of atheromatous plaque by adjusting Toll-Like Receptor (TLR) signaling pathways as well as peroxisome proliferator-activated receptors (PPARs), in order to delay atherosclerosis (AS) formation and stabilize atheromatous plaque [9, 10]. Chang et al. indicated that both the medicinal cake-separated moxibustion and direct moxibustion have a certain protective action on endothelial cells of the aorta in the rabbit of hyperlipidemia [9]. Yue et al. found that herb-partition moxibustion delays the formation of atherosclerosis through the inhibition of TLR4 expression [10]. This has provided a new strategy for the research on AS pathogenesis and prevention. In addition, based on clinical observation and systematic review of TCM literature, the selection of meridians and acupoints potentially having effect on hyperlipidemia treatment, has been studied and identified, which includes ten meridians (five *Yin* and five *Yang* meridians), and five acupoints (Stomach (ST), Spleen (SP), Ren (RN), Bladder (BL) and Pericardian (PC)) [11]. Based on these findings, several clinical studies on assessing medicinal cake-separated moxibustion have been undertaken, testing different acupoint prescriptions, medicinal-cake ingredients, treatment duration, etc., in attempt to identify an effective and standardized regimen [6, 12–16]. Most of these studies have shown possible therapeutic effects of the medicinal cake-separated moxibustion on hyperlipidemia, superior to the placebo or noninferior to statins.

In general, acupuncture and moxibustion is shown to be possibly effective in treating hyperlipidemia, with lower cost and fewer serious adverse events [17, 18]. However, due to the lack of robust study design and assessment methodology in existing clinical studies, the findings should be interpreted with caution. According to previous attempts on identifying an optimal regimen of acupuncture and moxibustion for treating hyperlipidemia, the warm needling acupuncture along with medicinal cake-separated moxibustion seems to be a modality that successfully combines the advantages of both acupuncture and moxibustion. This is worth further exploring to warrant its therapeutic effects [12, 15, 16]. So far, very few studies on this combined intervention are available. Hence, there is a need for a well-designed randomized control trial to validate the efficacy and safety of warm-needling acupuncture along with medicinal cake-separated moxibustion, by comparing it with statins.

### Hypotheses and objectives

#### Hypotheses

Warm needling acupuncture and medicinal cake-separated moxibustion (short as “acupuncture and moxibustion” in the following text) is noninferior to active control, in subjects with hypercholesterolemia, on° percent change of LDL-C° absolute change of LDL-C° percent change of HDL-C° percent change of TC° percent change of TG° rate of subject achieving LDL-C goal
Acupuncture and moxibustion is superior to active control, in subjects with hypercholesterolemia, on safety and tolerability° Adherence

#### Primary objectives

To evaluate the effect of 12 weeks of acupuncture and moxibustion compared with active control, on percentage change from baseline in low-density lipoprotein cholesterol (LDL-C) among those with hyperlipidemia.

#### Secondary objectives

To assess the effects of 12 weeks of acupuncture and moxibustion, compared to active control, in subjects with hypercholesterolemia, on° the absolute change in LDL-C,° the percent change in high-density lipoprotein cholesterol (HDL-C),° the percent change in total cholesterol (TC)° the percent change in triglyceride(TG)° the rate of subjects achieving LDL-C goal.
To evaluate the safety and tolerability of acupuncture and moxibustion, given for 12 weeks, in subjects with hypercholesterolemiaTo evaluate the adherence of acupuncture and moxibustion

### Trial design

This is a multicenter, open-label, randomized, stratified, active-controlled, noninferiority trial with two parallel groups. Randomization will be performed with a 1:1 allocation. Subjects with LDL-C values above the recommended level who meet the inclusion/exclusion criteria will be stratified based on their risk levels of heart disease [19, 20]. Then, they were instructed to follow the NCEP Adult Treatment Panel (ATP) [20] Therapeutic Lifestyle Change (TLC) diet first. After TLC is completed, subjects who have not reached the target lipid level will be randomly assigned to the treatments of either acupuncture and moxibustion or simvastatin. The duration of treatment for this study will be 12 weeks, followed by another 4 weeks for post-treatment assessment.

## Methods

The SPIRIT figure for schedule of enrolment (Fig. 1), interventions, and assessments of this study, and the SPIRIT Checklist are included as Additional file 1 of this protocol.

**Fig. 1 Fig1:**
[figure not shown]
SPIRIT Figure for schedule of enrolment, interventions, and assessments of the AMHRCTstudy

### Study setting

The study will include four sites in Hunan, China. They are First Affiliated Hospital of Hunan University of Chinese Medicine, Changsha Chinese Medicine Hospital, Yueyang Chinese Medicine Hospital, and Chenzhou Chinese Medicine Hospital. Other sites may be added for participation in the study. Sites that do not enroll any subjects within 3 months of site initiation will be closed. Each site must follow this study protocol; otherwise, it will be closed. The Steering Committee will audit and review the intervention performed in each site, to ensure that they are following this protocol.

### Inclusion criteria

To be included to the study, patients must:Provide informed consentBe male or female ≥18 to ≤75 years of ageHave a fasting triglyceride level ≤400 mg/dL (4.5 mmol/L) by central laboratory at screeningHave a fasting LDL-C as determined by central laboratory on admission and meeting the following LDL-C values based on risk factor (see Table 2 in Appendix 1) status [19, 20]:0–1 Risk Factor Group: LDL-C ≥160 mg/dl2+ Risk Factor Group: LDL-C ≥130 mg/dlCHD or CHD risk equivalents (see Table 3 in Appendix 1): LDL-C ≥100 mg/dl

### Exclusion criteria

Subjects are excluded from the study if they are diagnosed with one or more of the following conditions:Coronary heart disease (CHD) or CHD risk equivalent who are not receiving statin therapy with LDL-C at screening of ≤99 mg/dLHeart failure of New York Heart Failure Association (NYHA) class II, III or IV or last known left ventricular ejection fraction <30%Cardiac arrhythmia within 3 months prior to randomization that is not controlled by medicationMyocardial infarction, unstable angina, percutaneous coronary intervention (PCI), coronary artery bypass graft (CABG) or strokePlanned cardiac surgery or revascularizationType 1 diabetes;Newly diagnosed type 2 diabetes (within 6 months of randomization or new screening fasting plasma glucose ≥126 mg/dL (7.0 mmol/L) or HbA1c ≥6.5%), or poorly controlled type 2 diabetes (HbA1c >8.5%)Persistent systolic blood pressure (SBP) >160 mm Hg or diastolic BP (DBP) >100 mmHgThyroid stimulating hormone (TSH) < lower limit of normal (LLN) or TSH >1.5 × upper limit of normal (ULN), estimated glomerular filtration rate (eGFR) <30 ml/min/1.73 m^2^, aspartate aminotransferase (AST) or alanine aminotransferase (ALT) >2 × ULN, creatine kinase (CK) >3 × ULN (all at initial screening or at the end of lipid stabilization period(s) by the central laboratory)Known major active infection, or major hematologic, renal, metabolic, gastrointestinal or endocrine dysfunctionDeep vein thrombosis or pulmonary embolism within 3 months prior to randomization

Subjects are also excluded if they have taken any of the following medications for more than 2 weeks in the last 3 months prior to LDL-C screening: systemic cyclosporine, systemic steroids, isotretinoin (e.g., Accutane). Some anticoagulation treatments are also excluded (antiplatelet agents are permitted). Female subjects cannot be pregnant or be breastfeeding and premenopausal women must have to be willing to use at least one highly effective method of birth control during treatment and for an additional 15 weeks after the end of treatment.

### Recruitment

Each investigating site was chosen based on documentation for patient availability. Sites will utilize two main sources for identifying and recruiting potential subjects as described below:Incoming hyperlipidemia patients: the four sites in this study are famous for hyperlipidemia treatment in Hunan, China, thus the incoming patients aiming for hyperlipidemia treatments are the primary source for recruitmentAdvertisements: the participation opportunity to this study will be advertised widely in local newspapers and other publications that target hyperlipidemia treatments, in order to recruit enough participants in the recruiting period

### Interventions

All eligible subjects will be instructed to follow the NCEP Adult Treatment Panel (ATP) lifestyle-modification diet first [20]. This approach is designated therapeutic lifestyle changes (TLC). After TLC is completed, subjects who have not reached the target lipid level will be randomly assigned to the treatments of either acupuncture and moxibustion or simvastatin.

#### Therapeutic Lifestyle Change (TLC)

Subjects who meet the inclusion/exclusion criteria will initiate TLC. ATP III recommends a multifaceted lifestyle approach to reduce risk for CHD. Its essential features are:Reduced intakes of saturated fats (<7% of total calories) and cholesterol (<200 mg per day) (see Table 4 in Appendix 1 for overall composition of the TLC Diet)Therapeutic options for enhancing LDL lowering such as plant stanols/sterols (2 g/day) and increased viscous (soluble) fiber (10–25 g/day)Weight reductionIncreased physical activity

TLC adherence report form is made and sent to subjects to monitor their lifestyle change process. Re-assessment will be conducted after the TLC period.

#### Acupuncture and moxibustion versus simvastatin

According to the re-assessment of fasting lipid after TLC, a decision will be made on whether the lipid level has arrived at the target level (see Table 5 in Appendix 1) and whether subjects should continue with the intervention. For those who have not reached the target lipid level, they will be randomized in equal proportions between “acupuncture” and “simvastatin.”Acupuncture and moxibustionRationale for treatment:Warm-needling acupuncture and medicinal cake-separated moxibustion will be applied in the study which is guided by the approach of Traditional Chinese Medicine (TCM). The cake-separated moxibustion treatment belongs to the category of indirect moxibustion which applies moxibustion, herb and acupoints together. In this treatment, a drug-cake mixture is allocated upon selected acupoints, and then the lit moxa cone is placed onto the cake. In this case, the moxa-effect enhanced by the active components of the drug cake is allowed to penetrate through the skin and the acupoints.Based on the TCM theory that the heart is in charge of the blood circulation and blood vessels, some specific acupoints related to heart meridian and heart are selected, such as the *Shu* acupoint (RN14) and the *Mu* acupoint (BL15) of the heart meridian. BL18, BL20 and BL23 are used to tonify the spleen *Qi*, strengthen the liver *Qi* and also maintain the kidney *Qi*, as well as facilitate the conversion of lipids in the liver. ST40 and ST25, which belong to the stomach meridian and help the transformation function of spleen, can protect and work against hyperlipidemia by assisting the removal of phlegm from the body.Additionally, five Chinese herbal medicines are selected, including *Salviae Miltiorrhizae Radix* (*Dan shen*), *Crataegi Fructus* (*Shan zha*), *Curcumae Radix* (*Yu jin*), *Rhei Radix et Rhizoma* (*Da huang*), and *Alismatis Rhizoma* (*Ze xie*). They are able to activate the blood circulation, remove blood stasis and pain, clear away heart fire, remove irritability, nourish the blood and calm down the mind.In clinical practice, several studies with small sample sizes have assessed a variety of acupoint prescriptions, medicinal cake ingredients, treatment duration, etc. [12, 16]. Among these studies, Li et al. applied warm needling acupuncture on acupoints such as *Fenglong* (ST40, bilateral), *Zusanli* (ST36, bilateral), etc., once a day for 35 days, over a period of 12 weeks, showing a significant decrease in LDL-C, noninferior to statins [12]. Li et al. applied medicinal cake-separated moxibustion on two groups of acupoints, alternating over a period of 40 days with each group receiving 20 times of intervention [16]. This study demonstrated a remarkable decrease in LDL-C and TC, superior to the effect of a placebo. Meanwhile, Chang et al. have also examined effects of medicinal cake-separated moxibustion with different dosage upon blood fat and hemorheology in patients with hyperlipemia, showing that three moxa cones and five moxa cones both have therapeutic effect [17]. With these studies, so far we know, warm-needling acupuncture and cake-separated moxibustion are both effective for hyperlipidemia, respectively. Together with our previous clinical experiences on treating hyperlipidemia, we selected the studies mentioned above as pilot studies of this trial in determining the procedure course of the intervention.Needling/moxibustion details (demonstrated in Table 1)Treatment regimen:Interventions of warm-needling acupuncture and medicinal cake-separated moxibustion will be split into two groups. Group 1 (warm-needling acupuncture and medicinal cake-separated moxibustion) and group 2 (medicinal cake-separated moxibustion only) will alternate by week over the administration period (shown in Fig. 2), in order to avoid fatigue and nonresponse of acupoints due to constant stimulationPractitioners: registered acupuncturists who have completed post-secondary education on acupuncture, practiced acupuncture for more than 3 years, and passed the national qualification exam for Chinese medicine doctors

**Table 1 Tab1:** Needling and acupuncture details

Warm needling acupuncture (needle + moxa stick)	
Acupoints	*Fenglong* (ST40, bilateral), *Zusanli* (ST36, bilateral), *Sanyinjiao* (SP6, bilateral)
Depths of insertion	*Fenglong* (ST40) for 1.0 to 2.0 cun, *Zusanli* (ST36) and *Sanyinjiao* (SP6) for 1.0 to 1.5 cun (“cun” is a traditional Chinese measure using the width of a person’s thumb at the knuckle, whereas the width of the 2 forefingers denotes 1.5 cun and the width of 4 fingers (except the thumb) side-by-side is 3 cuns. Therefore, 1 cun may vary from person to person)
Needle stimulation	Manual manipulation
Responses elicited	*De qi* sensation
Needle retention time	30 min
Needle specifications	Sterile single-use acupuncture needles of 25–40 mm in length and 0.30 mm in diameter; manufactured by Suzhou Medical Supplies Co., Ltd., Suzhou, China
Moxibustion specifications	Small moxa stick, made of mugwort, with 1.5 cm length; manufactured by Suzhou Medical Supplies Co., Ltd., Suzhou, China
Manipulation	(1) locate and sterilize the acupoints; (2) insert the needles and stimulate to elicit response; (3) attach a small moxa stick to the needle tail and light the moxa stick; and (4) retain needles with moxa sticks for 30 min
Medicinal cake-separated moxibustion (medicinal cake + moxa cone)	
Acupoints	*Juque* (RN14), *Tianshu* (ST25, bilateral), *Pishu* (BL20, bilateral), *Xinshu* (BL15, bilateral), *Ganshu* (BL18, bilateral), *Shenshu* (BL23, bilateral)
Cake ingredients	*Dan Shen* (*Radix Salviae Miltiorrhizae*), *Shan Zha* (*Fructus Crataegi*), *Yu Jin* (*Radix Curcumae*), *Da Huang* (*Radix et Rhizoma Rhei*) and *Ze Xie* (*Rhizoma Alismatis*)
Cake preparation method	All cake ingredients in the same quantities were collected, ground into powder, mixed well with vinegar, and made into round, thin cakes of 1.5 cm in diameter, 3 mm in thickness and 3 g in weight; manufactured by Suzhou Medical Supplies Co., Ltd., Suzhou, China
Moxibustion specifications	Moxa cone, made of mugwort, with 1 cm in diameter; manufactured by Suzhou Medical Supplies Co., Ltd., Suzhou, China
Retention time	3 cones in total for 30 min
Manipulation	(1) locate the acupoints; (2) place the herbal cake on to the acupoints; (3) place a moxa cone onto the herbal cake and light the moxa cone; (4) renew the moxa cone once it is fully consumed, with 3 moxa cones in total per acupoint; and (5) retain herbal cakes with moxa cones for 30 min

**Fig. 2 Fig2:**
[figure not shown]
Treatment regimen flowchart. This figure demonstrates the treatment regimen and flowchart for intervention of warm needling and medicinal cake-separated moxibustionSimvastatinDosage: simvastatin (10 mg/day)AdministrationAll simvastatin tablets will be stored in the central pharmacy and assigned to each investigator site by a qualified staff. The drug will be administered orally to subjects at the investigator site by a physician or a nurse in accordance with instructions in the medication guidesSchedule: 7 days per week for 12 weeksDosage adjustment:there will be no dose adjustments in this study. If, in the opinion of the investigator, a subject is unable to tolerate a specific dose of simvastatin and requires dosage adjustment, that subject will discontinue simvastatin but will continue to return for all other study procedures and measurements until the end of the study

### Discontinuity of intervention

Subjects in the study are able to withdraw from the study at any time, either partially or entirely.

When a subject fully consents to withdrawal from the study, the subject will no longer receive the investigational treatment and will have the right to discontinue any further involvement in the study, including any format of follow-up. Below is a list of reasons for discontinuing intervention:Withdrawal of full consent from subjectSubject requests the ending of investigational interventionAdministrative decision by the principal investigatorUnanimous decision by the principal investigator/physicianPregnancy in a female subjectAdverse event (e.g., serious adverse event related to the intervention)

### Concomitant medication

The following treatments are not permitted during the study:Prescribed lipid-regulating medications other than acupuncture and moxibustion or simvastatin, such as fibrates and derivatives, bile-acid sequestering resinsRed yeast rice, niacin >200 mg per day, omega-3 fatty acid (e.g., DHA and EPA) >1000 mg per day. Any other drug that significantly affects lipid metabolism (e.g.,, systemic cyclosporine, systemic steroids (administered intravenously (IV), intramuscularly (IM), or per os (PO)), vitamin A derivatives and retinol derivatives for the treatment of dermatologic conditions (e.g.,, Accutane)). Vitamin A as part of a multivitamin preparation is permitted.Prescribed amphetamines, or amphetamine derivatives, and weight-loss medications

Besides, simvastatin or foods that are known potent inhibitors of CYP3A (itraconazole, ketoconazole, and other antifungal azoles, the macrolide antibiotics erythromycin, clarithromycin, and the ketolide antibiotic telithromycin, HIV protease inhibitors, the antidepressant nefazodone and grapefruit juice in large quantities (more than 1 quart daily)) should not be used during the study, because of their potential impacts on the metabolism of certain statins.

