### Sample size

A significance level of 0.95 and a power of 0.80 will be allocated for the calculation of sample size. In accordance with a previous study [17], we could employ an effect size of 0.343 on absolute value change of LDL-C value, and a standard deviation of 0.7. In this case we estimate that the sample size for the acupuncture group and active control group should be approximately 65, respectively. The total sample size needed is 130.

In case of missing observation and patients lost, we assume that 90% of subjects will remain in the study. Thus, the sample size for two groups should be roughly 70 for each group.

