### Statistical methods

#### Dataset analysis

For the primary endpoint of percentage change in LDL-C from baseline, the efficacy of acupuncture and moxibustion will be evaluated at week 12 by comparing the treatment effect to that of the active control group. A type I error of 0.05 will be allocated to the test.

There are three main analysis sets:Full analysis set (FAS): includes all randomized subjects who have received at least 1 investigational treatmentCompleter Analysis Set (CAS), includes subjects in the FAS who completed their scheduled intervention and have a nonmissing LDL-C value at week 12Effect Durability Analysis Set (EDAS), includes subjects in the FAS who completed their scheduled intervention and have non-missing LDL-C values at week 6 and week 12

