#### Statistical analysis plan

The primary analysis set for the primary endpoint is the FAS. It is to use the repeated measures, linear mixed-effects model, including terms for treatment group, stratification factor, baseline LDL-C, scheduled visit and the interaction of treatment with scheduled visit. Missing values will not be imputed when the repeated measures, linear mixed-effects model is used.

We will use the chi-squared test for binary outcomes, and the *t* test for continuous outcomes. For subgroup analyses, we will use regression methods with appropriate interaction terms (respective subgroup treatment group). Multivariable analyses will be based on logistic regression for binary outcomes and linear regression for continuous outcomes. We will examine the residual to assess model assumptions and goodness-of-fit. For timed endpoints, such as mortality, we will use the Kaplan-Meier survival analysis followed by the multivariable Cox proportional hazards model for adjusting for baseline variables. We will calculate Relative Risk (RR) and RR Reductions (RRR) with corresponding 95% confidence intervals to compare dichotomous variables, and difference in means will be used for additional analysis of continuous variables. *P* values will be reported to four decimal places with *P* values < 0.05 reported as *P* < 0.05. Up-to-date versions of R (R Foundation) will be used to conduct analyses. For all tests, we will use two-sided *P* values with alpha no greater than 0.05 level of significance. We will use the Bonferroni method to appropriately adjust the overall level of significance for multiple primary outcomes, and secondary outcomes.

In investigation of the robustness of the analysis results, the primary analysis will be repeated using the CAS. In addition, parametric analysis of covariance (ANCOVA) and appropriate nonparametric methods will be used on the FAS, in which missing data will be imputed using the last-observation-carried-forward (LOCF) approach. The primary analysis will also be repeated for subgroups of interest.

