However, certain limitations still exist in this study. One is the absence of a placebo control group due to the limited study budgets. Because of this lack of comparison, it may not be able to determine whether the outcome observed is due to the therapeutic effect of acupuncture and moxibustion or its placebo effect, if acupuncture and moxibustion is proved to be inferior to simvastatin. Nevertheless, judgment from clinical experiences and relevant findings from previous studies can help in identifying and justifying the effect with clinical significance.

Another limitation is the absence of blinding in patients and health care providers due to the operation characteristics of acupuncture and moxibustion. With patients knowing their intervention assignments after randomization, there may be a potentially higher possibility of cross-over between and drop-off from these two arms; thus, the potential selection bias may occur. But detailed explanation can be given to patients on these two arms of interventions in order to inform potential effects and safety in both arms. This will help limiting the drop-off and cross-over rates. Moreover, with the intervention assignment revealed, the effect identified from the acupuncture and moxibustion group may not fully result from its therapeutic aspect but a psychological aspect. But the outcome measures examined in this study are all objective – based on the fasting lipid level; and in the analysis process intervention assignment is fully blinding to data assessors. Therefore, the information bias due to lack of blinding could be controlled to a considerable extent.

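### The medication rules do not tie simvastatin use to arm, and neither analysis set removes an acupuncture subject who adds simvastatin, which biases toward noninferiority

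*Protocol article*

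**What the plan says.** All places are in the Protocol article.

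- **Concomitant medication, first list.** The drugs not permitted are "Prescribed lipid-regulating medications other than acupuncture and moxibustion or simvastatin", with fibrates and resins as examples. The exemption for simvastatin names no arm.
- **Concomitant medication, next paragraph.** It tells subjects to avoid "simvastatin or foods that are known potent inhibitors of CYP3A". Azoles, macrolides, protease inhibitors, nefazodone and large amounts of grapefruit juice follow. Again no arm is named.
- **Acupuncture and moxibustion versus simvastatin.** The control arm takes simvastatin daily for the 12 weeks, given at the site by clinical staff from centrally held stock.
- **Exclusion criteria.** Statin therapy appears once, in a criterion on "Coronary heart disease (CHD) or CHD risk equivalent who are not receiving statin therapy with LDL-C at screening" at or below 99 mg/dL. Statins are not among the earlier drugs that exclude a subject (cyclosporine, steroids, isotretinoin).
- **Dataset analysis.** The full analysis set (FAS) takes everyone randomized and treated at least once. The completer set (CAS) takes FAS members who finished the planned course and have a week-12 LDL-C. Neither definition mentions other medication.
- **Statistical analysis plan.** The FAS is primary, and the primary analysis is repeated on the CAS as a robustness check.
- **Discussion.** On the lack of blinding, the article expects that "there may be a potentially higher possibility of cross-over between and drop-off from these two arms". The remedy offered is explanation to patients.

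**The concern.** In a noninferiority trial, anything that makes the arms alike helps the trial reach its hoped-for conclusion. Use of the comparator drug in the experimental arm is the plainest case, and here the text leaves it open. Read alone, the first medication rule lets an acupuncture subject take simvastatin. The second rule contradicts the first and, taken literally, also the control regimen, so a site cannot derive a consistent instruction from the section.

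A completer or per-protocol analysis normally backs up the full analysis set against this. Here the completer set is defined by course completion and an available week-12 value. An acupuncture subject who attends every session and also takes simvastatin meets both conditions. The two analyses could then agree with each other and share the same bias.

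The status of subjects on a statin at screening is a related gap. Baseline is the day-1 value after the lifestyle period. If a statin is on board or being withdrawn then, later change in LDL-C partly reflects that.

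**Working it through.** **1. What each rule does with simvastatin, by arm**

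| Place | Acupuncture arm | Simvastatin arm |
|---|---|---|
| Concomitant medication, first list | exempt from the ban | exempt from the ban |
| Concomitant medication, next paragraph, read literally | not to be used | not to be used |
| Control regimen | not addressed | taken daily for 12 weeks |
| Exclusion criteria | prior statin use does not exclude | prior statin use does not exclude |

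The first two rows conflict in both arms, and the second and third conflict in the control arm. Correcting the second row to medications would remove both conflicts, but the first row would still have no arm restriction.

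**2. Who stays in which analysis set**

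| Acupuncture subject who | FAS | CAS |
|---|---|---|
| abandons acupuncture for simvastatin | stays | leaves (course not finished) |
| adds simvastatin, finishes the course, has a week-12 value | stays | stays |

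The adherence rate under Secondary outcomes counts treatments given over treatments planned, so the second subject can score 100%.

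**3. Reproducing the plan's sample size**

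Inputs: "A significance level of 0.95 and a power of 0.80 will be allocated for the calculation of sample size" (0.95 read as the confidence level), "A type I error of 0.05 will be allocated to the test", "For all tests, we will use two-sided" P values, and "we could employ an effect size of 0.343 on absolute value change of LDL-C value, and a standard deviation of 0.7".

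n per arm = 2 × [SD × (z for two-sided 0.05 + z for power 0.80) / difference]²
= 2 × [0.7 × (1.960 + 0.842) / 0.343]² = 65.4, rounded up to 66.

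The plan says about 65. A noninferiority calculation with margin 0.343, true difference 0 and one-sided 0.025 gives the same 66. One-sided 0.05 gives 52, which does not match. The figures are therefore consistent with one-sided 0.025, used below. Power at 65 per arm is 79.8%.

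**4. Illustration of contamination**

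Assumptions, none of them stated in the document:
- noninferiority margin 0.343 (the article calls this an effect size and gives no margin);
- true deficit of acupuncture exactly at that margin;
- a share c of the acupuncture arm takes simvastatin and gets its full effect;
- c of 10%, 20% or 30%.

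SE = 0.7 × √(2/65) = 0.1228.
Expected difference = 0.343 × (1 − c).
P(false noninferiority) = Φ(0.343c / SE − 1.96).

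| c | Expected difference | 0.343c / SE | P, 65 per arm | P, 63 per arm |
|---|---|---|---|---|
| 0% | 0.343 | 0 | 2.5% | 2.5% |
| 10% | 0.309 | 0.279 | 4.6% | 4.6% |
| 20% | 0.274 | 0.559 | 8.1% | 7.9% |
| 30% | 0.240 | 0.838 | 13.1% | 12.8% |

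The last column uses 70 × 0.90 = 63, from the plan's inflated size and 90% retention. The illustration is on absolute LDL-C change, the scale of the sample-size section. The primary outcome is percentage change.

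**5. Prior statin use**

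If a statin is continued in both arms, the contrast shrinks, which favours noninferiority. If it is stopped at randomization in the acupuncture arm, LDL-C there rises, which works against noninferiority. The text does not say which would happen, so no direction follows.

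**The case against.** - **The apparent ban on simvastatin is an evident slip.** The sentence concerns CYP3A inhibitors, its list does not include simvastatin, and its stated reason is the metabolism of statins. A reader might infer that the protocol forbids its own control drug. The regimen section shows that it does not. This stands, and what remains is a wording conflict to correct.
- **The exemption names the two study treatments together**, and each subject is assigned to one. That is probably the intent. The sentence still does not say so, and correcting the slip would not supply the restriction.
- **There are safeguards.** Staff give trial simvastatin at the site. Appendix 2 (Lipid Measurements) conceals post-randomization lipid values and discourages extra lipid panels, which removes a main reason to add a statin. Other prescribed lipid-regulating drugs are barred. This stands and narrows the route, but leaves outside simvastatin prescriptions and continued prior use open.
- **Crossovers leave the completer set.** A reader might infer that this set keeps all of them. It does not: a subject who abandons the assigned treatment has not finished the course. Only add-on use survives the definition.
- **Detail may sit in a document not shown.** Washout rules or fuller per-protocol exclusions may be there. That is why the point rests on the stated rules and the stated set definition, not on absent detail.

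**Conclusion.** The point holds in a limited form. The simvastatin wording is inconsistent and not tied to arm, subjects on a statin at screening are not excluded, and both the primary set and the robustness set keep an acupuncture subject who adds simvastatin and completes the course. For that subject the bias runs toward noninferiority.

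Two stronger conclusions are not supported. The first is that the trial's false-noninferiority rate is 4.6% to 13.1%. Those figures rest on an assumed margin, a true deficit placed exactly at it, a full simvastatin response and assumed contamination rates. The article expects crossover but gives no rate. The figures show only how sensitive the error rate is to modest contamination. The second is that statin use at screening itself produces false noninferiority. Its direction depends on what happens to the statin afterwards, and randomization should balance prior use on average.

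The defect in the text is certain and its effect on the result is not. The correction is cheap and should be made.

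**What to change.** 1. **Reconcile the passages.** Concomitant medication, the simvastatin regimen and the Exclusion criteria should together state once, without conflict, which lipid-lowering drugs apply in each arm and the status of subjects on a statin at screening. The clinical rule is for the sponsor.
2. **Record lipid-lowering drug use with start and stop dates**, from screening to the end of follow-up. Concomitant therapy is already collected at screening.
3. **Amend the completer (or per-protocol) set** to exclude anyone who used a lipid-lowering drug outside the assigned arm. Keep the FAS as the primary set, and report the number excluded by arm.

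A covariate for prior statin use is optional.

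The cost is a wording amendment, one derived variable and a smaller completer set. At 10% contamination of a 65-subject arm the loss would be 0.10 × 65 = 6.5, that is 6 or 7 subjects. Because the exclusion depends on behaviour after randomization, the amended set is a check on the FAS result and does not replace it.
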